**Follow up assessment will be performed on week 2 and weeks 4, 7, 10, 14 and 18 and will include:**

Physical exam, vital signs, computerized cognitive tests (at week 10), questionnaires, record of AEs related or not related to the medication assignment, pill counts, blood samples.

**Interventions:**

Our participants will be free of hepatic, as well as renal impairment. The recommendation from the FDA is to obtain liver function tests prior to starting the drug and again should symptoms such as rash or hepatitis occur. This rather rare adverse reaction tends to occur at about one month after starting the medication (in less than 4% on the drug or placebo), so the investigators will obtain a bilirubin and transaminases at the planned 1-month follow up.

Adverse events related to the medication assignment, to rehabilitation practice or to other causes will be adjudicated by the safety committee with input from the principal investigator.

Patients will be contacted weekly by phone to help maintain interest in the trial, assure use of the assigned medication, and ask about possible adverse reactions. The coordinator will obtain this information and provide the feedback using a standard script and checklist.

**Quality control and analysis:**  All patient records and specimens will be tracked in a manner consistent with Good Clinical Practice by a quality-controlled, auditable, and appropriately validated laboratory information management system, to ensure compliance with data confidentiality as well as adherence to authorized use of specimens as specified in this protocol and in the Informed Consent Form.

**Statistical Analysis**

Safety analysis (Primary Endpoint): All safety data will be summarized in appropriate tables.

AEs will be coded according to coding dictionaries (MedDRA version 22.0 or higher) and presented in tables by System Organ Class (SOC) and Preferred Term (PT) and by treatment group. Safety will be also assessed by evaluating findings of physical examinations, vital signs, clinical laboratory test results, concomitant medications by treatment group. The changes from baseline in vital signs, clinical laboratory tests results will be displayed.

**Efficacy Assessments**

Primary outcomes analyses:

Stage 1- The Paired T-test or Signed rank test for two means (as is appropriate) will be applied for testing the statistical significance of the difference in depressive scores and in functional scores from baseline to week 10 and week 18.

Secondary outcome analyses:

Stage 1 - The Paired T-test or Signed rank test for two means (as is appropriate) will be applied for testing the statistical significance of the difference in scores from baseline to week 10 and week 18.

Pairwise comparisons of the study day assessments to baseline for significant main effects and interactions will be performed with Bonferroni corrections for multiple comparisons.

the effect of Maraviroc over time will be analyzed with repeated measures ANOVAs, with time as a within-subjects factor and depression scores (as measured by the MADRS) as the dependent variables. Associations between numeric variables will be determined using Spearman’s rank correlation analysis (coefficient estimate r).

Response rate will be defined as a ≥ 50% decrease from baseline depression scale scores to the trial endpoint. Significance will be evaluated at the α =.05 level, two-tailed, after Greenhouse-Geisser corrections.

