### Interventions

Participants will be outpatients diagnosed with PSD up to 12 months after the index event. Following baseline assessments, all participants will receive the active treatment - Maraviroc 300 mg once daily for 10 weeks in an open-label design. They will be followed for another 8 weeks after cessation of Maraviroc. The study intervention will be given as add-on therapy to the patient’s usual prescribed care (treatment as usual),thus all participants will continue their existing antidepressant treatment without change. All participants will be instructed to continue their usual treatment for the whole trial duration. Endpoints:

Primary Safety Endpoint: No serious treatment-emergent adverse events (TEAEs), no TEAEs leading to discontinuation.

Primary Efficacy Endpoint: The primary efficacy evaluation will be the MADRS total score as measured by the change from baseline (i.e., Day 1 pre-dose) to Week 10.

Secondary Endpoints: • Proportion of responders • Proportion of subjects in remission • Change from baseline to week 10 in subject-reported depressive symptoms using the QIDS-SR16. • Change from baseline to week 10 in severity of illness using the CGI-S and CGI-I. • Change from baseline to week 10 in severity of illness using the PGI-S and PGI-C. • Change from baseline to week 10 in anxiety symptoms, as measured by the GAD-7. • Change from baseline to week 10 in the SIS, ADL, and RNL scores.

Neuroimaging acquisition and processing A magnet resonance imaging (MRI) protocol will be performed before visit 1 and will consist of previously described pulse sequences ^36^. All axial slices will be prescribed on the same orientation, covering the whole brain, aligned along the fourth ventricle-orbitofrontal orientation. MRI analyses will include assessment of white matter (WM) hyperintensities, tissue segmentation and Brain atrophy measures as we have previously described^36^.

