**Prohibitions and Restrictions**

- Potent CYP3A4 inhibitors are not permitted within 1 week or within a period less than 5 times the drug’s half-life, whichever is longer, before the first dose of study medication and throughout the study.
- Potent CYP3A4 inducers are not permitted for 30 days prior to the first dose of study medication and throughout the study.

Safety Evaluations

Physical examination, body weight, vital signs, 12-lead ECG, clinical laboratory tests, and evaluation of adverse events and concomitant therapies will be performed throughout the study to monitor subject safety. Suicidal ideation and behavior will be assessed by a psychiatrist, as well as continuous follow-up of mental state and adverse events after cessation of Maraviroc treatment.

Primary Efficacy Measures:

**MADRS** -The 10-item clinician-administered MADRS was designed to be used in subjects with MDD to measure the overall severity of depressive symptoms (Montgomery and Asberg 1979). The MADRS has been validated, is reliable, and is acceptable to regulatory health authorities as a primary scale to determine efficacy in major depression. The structured interview guide for the Montgomery Asberg Depression Rating Scale (SIGMA) will be used for each administration (Williams 2008). Using structured interview guides have previously been shown to increase the reliability of given scales. In depression, ‘response’ is commonly defined as a ≥50% reduction in the initial symptom score and remission is typically defined as a total score of ≤10 (Montgomery 1994). The primary efficacy evaluation will be the change from baseline in the MADRS total score in the treatment phase.

Secondary Efficacy measures:

**QIDS-SR16** - The patient administered 16-item quick inventory of depressive symptoms- self report (QIDS-SR16) is designed to be used in patients with MDD to measure the overall severity of depressive symptoms (Rush 2003; Trivedi 2004).

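### The primary efficacy analysis tests several depressive and functional scores at weeks 10 and 18, although the protocol names MADRS change to week 10 as the only primary efficacy endpoint

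*Protocol*

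**What the plan says.** The Endpoints text (Protocol, Interventions) is specific: "The primary efficacy evaluation will be the MADRS total score as measured by the change from baseline (i.e., Day 1 pre-dose) to Week 10". The same list places the week-10 changes in QIDS-SR16, SIS, ADL and RNL among the secondary endpoints. The paragraph on primary efficacy measures agrees on the scale and confines it to treatment: "The primary efficacy evaluation will be the change from baseline in the MADRS total score in the treatment phase". The treatment phase ends at week 10.

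The primary outcomes analyses under Efficacy Assessments are broader. A paired t-test or signed rank test is applied to "the difference in depressive scores and in functional scores from baseline to week 10 and week 18". No scale is singled out and neither time point takes precedence.

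The one multiplicity provision stands under the secondary outcome analyses: "Pairwise comparisons of the study day assessments to baseline for significant main effects and interactions will be performed with Bonferroni corrections for multiple comparisons". The significance level is given once, at the end of the section: "Significance will be evaluated at the α =.05 level, two-tailed, after Greenhouse-Geisser corrections".

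The section also says: "Response rate will be defined as a ≥ 50% decrease from baseline depression scale scores to the trial endpoint". The Objectives section defines response as a fall of at least 50% in MADRS total score.

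**The concern.** The sections disagree about what the primary efficacy test is. A reader of the Endpoints text expects one p-value. A reader of the statistical section can expect up to nine, some of them from a visit 8 weeks after treatment stopped, and any of them could later be presented as the primary efficacy finding. In an uncontrolled study of 10 patients, that freedom matters to whoever uses the result to plan the continued efficacy research that the Design section foresees. The looser response wording adds a smaller ambiguity: the trial endpoint could be week 10 or week 18, so responder status could depend on which is chosen.

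**Working it through.** The protocol gives no family-wise error rate, so there is no stated figure to reproduce.

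**Step 1. Set the texts side by side.**

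| Feature | Endpoints and primary efficacy measures | Primary outcomes analyses |
|---|---|---|
| Scale | MADRS | depressive scores and functional scores |
| Time | week 10 (treatment phase) | week 10 and week 18 |
| Number of tests | 1 | several, unordered |
| Correction | not needed | none |

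The Bonferroni sentence does not close the gap. It stands under the secondary analyses and concerns comparisons of study days with baseline that follow significant main effects and interactions, which is a follow-up to the repeated-measures ANOVA. It does not reach the primary paired tests.

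**Step 2. Count the tests that Table S1 allows.** The protocol names three depressive scales (MADRS, QIDS-SR16, GDS) and three functional scales (SIS, ADL, RNL). Table S1 schedules GDS, SIS and RNL on Day 1 and at weeks 14 and 18, but not at week 10.

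- Weeks 10 and 18: MADRS, QIDS-SR16, ADL, giving 3 × 2 = 6 tests.
- Week 18 only: GDS, SIS, RNL, giving 3 tests.
- Total: 9 tests.
- If depressive scores means MADRS alone: MADRS × 2, ADL × 2, SIS, RNL = 6 tests.

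**Step 3. Chance of at least one p < 0.05 under the global null, independent tests.** The formula is 1 − 0.95^k.

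- k = 1: 5%.
- k = 6: 1 − 0.95^6 = 0.265, about 26%.
- k = 9: 1 − 0.95^9 = 0.370, about 37%.

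For favourable results only, each two-sided test contributes 0.025. With k = 9, 1 − 0.975^9 = 0.204, about 20%.

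**Step 4. Allow for correlation.** The protocol gives no correlations, so a common value from 0 to 0.8 was assumed. Two-sided paired t-tests with n = 10 were simulated under the null (60,000 runs) for 9 tests:

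| Assumed correlation | Either direction | Favourable only |
|---|---|---|
| 0 | 36.7% | 20.5% |
| 0.3 | 33.4% | 17.0% |
| 0.5 | 28.3% | 14.2% |
| 0.7 | 22.2% | 11.2% |
| 0.8 | 18.4% | 9.1% |

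The first row agrees with the exact values in Step 3. Correlations structured by domain and visit (same domain 0.3–0.7, other domain 0.1–0.4, across time 0.5–0.7) gave 27% to 35% in either direction, inside this range.

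**Step 5. After correction.** One test, MADRS at week 10, has an error rate of 5%. Keeping all nine as primary with Bonferroni would need 0.05/9 = 0.0056 per test, with a family-wise rate of 1 − (1 − 0.0056)^9, about 4.9%, under independence.

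**The case against.** The best defence is that the mismatch is loose wording in a small safety study. The primary objective and the primary endpoint of the statistical section are safety, and the sample size does not depend on any efficacy test. The ANOVA sentence itself specifies MADRS as the depression score, and QIDS-SR16 and GDS are described under secondary measures, so depressive scores may mean only MADRS. The alpha sentence mentions Greenhouse-Geisser, so it may have been written for the ANOVA rather than the paired tests. These points stand. They lower the priority and support showing the 6-test count beside the 9-test count. They do not explain why functional scores and week 18 appear in a primary analysis.

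Four stronger readings are tempting, and the protocol does not support them.

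- **A false-success rate of 30% to 45%.** The upper end comes from about 12 independent tests (1 − 0.95^12 = 46%). Table S1 has no week-10 GDS, SIS or RNL, the scales are related and measured in the same patients, and the rate counts significant worsening as well as improvement. Nor does any rule in the protocol equate one significant score with success.
- **No multiplicity control at all.** There is a Bonferroni provision; its stated scope does not extend to the primary tests.
- **An undefined response scale.** The Objectives section already fixes it as MADRS. Only the week is open.
- **Loss of patients through the repeated-measures ANOVA.** The protocol states no complete-case rule, and the handling of missing data may properly sit in a statistical analysis plan that is not shown.

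**Conclusion.** The contradiction is real: one primary efficacy endpoint is named in two places, and a wider, uncorrected set of tests is labelled primary in a third. If all tests feasible under Table S1 are read as primary, the chance of at least one nominally significant primary efficacy result under the null is about 18% to 37% for 9 tests, and at most 26% for 6, against 5% for the single named test. In the favourable direction only, it is about 9% to 20% for 9 tests, against 2.5%.

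These figures assume that each paired test is done at two-sided 0.05, that no true change exists on any scale, and that correlations lie between 0 and 0.8. They measure the chance of a nominally significant result, not of a declared trial success. Because safety is the primary objective, the point should be fixed but is not critical; the safety endpoint and the sample size are unaffected.

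**What to change.** Under Efficacy Assessments:

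1. Limit the primary efficacy analysis to a single paired test of MADRS total score, Day 1 to week 10, at two-sided 0.05.
2. Label all other scales, and every week-18 comparison including MADRS, as secondary. Either adjust them for multiplicity (Holm or Bonferroni over a listed set) or report them descriptively with 95% confidence intervals.
3. Align the response sentence with the Objectives section: a fall of at least 50% in MADRS total score from Day 1, assessed at week 10.

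This changes analysis wording only, with no added visits, patients or data. The cost is fewer nominally significant results to report.

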**SAFETY PLAN**

Several measures will be taken to ensure the safety of patients participating in this study. Eligibility criteria have been designed to exclude patients at higher risk for toxicities. Patients will undergo safety monitoring during the study, including assessment of the nature, frequency, and severity of AEs. Investigators will assess the occurrence of AEs and serious AEs at all patient evaluation time-points during the study. All AEs and serious AEs, whether volunteered by the patient, discovered by study personnel during questioning, or detected through physical examination, laboratory test, or other means, will be recorded in the patient’s medical record and on the appropriate case report forms, as well as appropriately reported.

